## Abstract

**Background:**

Patients with idiopathic carpal tunnel syndrome (CTS) are commonly treated with steroid injection into or proximal to the carpal tunnel. However, evidence for its efficacy beyond one month has not been established in randomized placebo-controlled trials. The primary aim of this randomized trial is to assess the efficacy of steroid injection into the carpal tunnel in relieving symptoms of CTS in patients with symptoms of such severity to warrant surgical treatment but have not been treated with steroid injection.

**Methods/Design:**

The study is a randomized double-blind placebo-controlled trial. Patients referred to one orthopedic department because of CTS are screened. Eligibility criteria are age 18 to 70 years, clinical diagnosis of primary idiopathic CTS and abnormal nerve conduction tests or clinical diagnosis made independently by two orthopedic surgeons, failed treatment with wrist splinting, symptom severity of such magnitude that the patient is willing to undergo surgery, no severe sensory loss or thenar muscle atrophy, and no previous steroid injection for CTS. A total of 120 patients will be randomized to injection of 80 mg Methylprednisolone, 40 mg Methylprednisolone, or normal saline, each also containing 10 mg Lidocaine. Evaluation at baseline and at 5, 10, 24 and 52 weeks after injection includes validated questionnaires (CTS symptom severity scale, *Quick*DASH and SF-6D), adverse events, physical examination by a blinded assessor, and nerve conduction tests. The primary outcome measures are change in the CTS symptom severity score at 10 weeks and the rate of surgery at 52 weeks. The secondary outcome measures are the score change in the CTS symptom severity scale at 52 weeks, time to surgery, and change in *Quick*DASH and SF-6D scores and patient satisfaction at 10 and 52 weeks. The primary analysis will be carried out using mixed model analysis of repeated measures.

**Discussion:**

This paper describes the rationale and design of a double-blind, randomized placebo-controlled trial that aims to determine the efficacy of two different doses of steroid injected into the carpal tunnel in patients with moderately severe idiopathic CTS.

**Trial registration:**

Clinicaltrials.gov identifier NCT00806871

## Background

Carpal tunnel syndrome (CTS) is the most common peripheral compression neuropathy in the upper extremity with a prevalence of 3.7% in the adult general population [1]. The prevalence of persons who have moderate or severe CTS but have not sought care or been diagnosed correctly is almost 1% in the general population [2]. CTS of mild severity is commonly treated with wrist splint but for moderately severe symptoms surgical treatment is often required [3]. Carpal tunnel release is one of the most common surgical procedures; the annual incidence in a US population (2001-2005) was 134 per 100,000 [4]

Although carpal tunnel release has been shown to produce good outcomes regarding relief of symptoms caused by CTS [5], it has several disadvantages including surgery-related pain and hand weakness [6]. These are common problems and may last several months after surgery. Other less common complications include wound infection, chronic regional pain syndrome, and nerve injuries [7,8]. In addition, surgery is associated with direct costs as well as indirect costs related to work absence after surgery because the majority of patients require sick leave for a varying length of time depending on the degree of postoperative morbidity and the type of work [9]. The median time of work absence has been 4 weeks in several studies, with a proportion of patients having long-term work disability [9]. The economic impact of work absence following surgery for CTS can be substantial both for the patients and the society. Consequently avoiding sick leave would be an important advantage for nonsurgical treatment.

Although many alternatives to surgery have been proposed there is little evidence to support the efficacy of most of these treatments [10]. Steroid injection into or proximal to the carpal tunnel is widely practiced in the treatment of patients with idiopathic CTS particularly in the United States [11]. However, the evidence for its efficacy beyond one month has not been established in placebo-controlled trials. In a recent Cochrane review of local corticosteroid injection for CTS, the authors concluded that there was evidence supporting clinical improvement at one month compared to placebo but no significant improvement after 8 weeks compared to nonsteroidal anti-inflammatory drugs or wrist splint [12]. None of the studies reviewed involved a double-blind comparison with a follow-up of more than one month.

Because of the strong evidence supporting the efficacy of surgery, randomized studies that compared steroid injections with surgery may provide indirect measure of the efficacy of steroid injection. One such study of 163 wrists comparing surgery with steroid injection (84% received 2 injections within 2 weeks) reported similar effects up to 1 year but outcomes were not assessed with validated CTS-specific measures and it did not compare the full effect size of surgery with that of steroid injection as the primary outcome but rather the proportion of patients in each group that achieved modest improvement [13]. Previous studies comparing steroid injection with surgery have not specifically involved patients whose CTS was of such severity that surgery was clearly indicated. Obviously, if the study population includes many patients with less severe CTS the comparison may be biased. Because the main effects of treatment are improvements in symptoms and in hand function it is important that these outcomes be evaluated with reliable and valid measures [14,15]. The use of steroid injection as a routine treatment in patients with CTS would incur costs and, if ineffective, would prolong patients' disability and delay surgery that usually results in rapid symptom improvement.

In patients with CTS secondary to rheumatoid arthritis the use of steroid injection is based on the assumption that flexor tenosynovitis is the causative factor. This is probably the theoretical basis for using steroid injection even in idiopathic CTS although no such etiological relationship has been established. To our knowledge, the efficacy of local steroid injection in CTS has not been investigated in randomized trials with regard to the possible presence of a dose-response relationship.

There is currently no evidence to support the efficacy of carpal tunnel steroid injection in relieving symptoms of idiopathic CTS for up to 1 year as measured with validated CTS-specific symptom measures and no evidence of possible dose-response relationship.

## Methods/Design

### Design

The trial is a prospective randomized double-blind placebo-controlled dose-response clinical trial comparing injection of 40 mg Methylprednisolone, 80 mg Methylprednisolone or placebo into the carpal tunnel in patients with moderately severe idiopathic CTS not previously treated with steroid injection.

### Inclusion Criteria

The inclusion criteria (Table 1) are primary, idiopathic CTS, age 18 to 70 years, either gender, symptoms of classic or probable CTS according to the diagnostic criteria in the Katz hand diagram [16], symptom duration of at least 3 months, inadequate response to wrist splint, nerve conduction tests showing median neuropathy at the wrist and no other abnormalities or, in the presence of normal nerve conduction test results, two orthopedic surgeons independently diagnose the patient with CTS, and symptom severity of such magnitude that the patient is willing to undergo surgery.

**Table 1 T1:** Eligibility criteria

Inclusion criteria	Exclusion criteria
Primary, idiopathic CTS	Previous steroid injection in same wrist
Age 18-70 years	Inflammatory joint disease
Either gender	Diabetes mellitus
Classic or probable CTS according to the diagnostic criteria in the Katz hand diagram	Polyneuropathy
Symptom duration of at least 3 months	Vibration induced neuropathy
Inadequate response to wrist splint	Pregnancy
Abnormal nerve conduction tests or, if normal, CTS diagnosed independently by 2 surgeons	Trauma to affected hand in preceding year
Patient willing to undergo surgery	Previous surgery for CTS on affected hand
	Surgery for CTS on contralateral hand in preceding 2 months
	Inability to respond to questionnaires
	Severe sensory loss (two-point discrimination >8 mm)
	Thenar atrophy
	Severe medical illness
	Drug or alcohol abuse

### Exclusion Criteria

The exclusion criteria are previous steroid injection for CTS in the same wrist, severe sensory loss (two-point discrimination exceeding 8 mm), thenar atrophy, inflammatory joint disease, diabetes mellitus, vibration-induced neuropathy, polyneuropathy, pregnancy, trauma to the affected hand in the previous year, previous surgery for CTS in the affected hand, surgery for CTS in the contralateral hand within the past 2 months, inability to respond to questionnaires (e.g., because of language difficulty or cognitive impairment), severe medical illness, and known abuse of drugs or alcohol.

### Recruitment

Patients referred by primary care physicians to one orthopedic department (Hässleholm and Kristianstad Hospitals) are examined by trial investigators (orthopedic surgeons) at the outpatient clinic and screened for eligibility. Those with a clinical diagnosis of CTS who have failed treatment with wrist splint and whose symptom severity is judged to warrant surgery are offered to be put on the waiting list for carpal tunnel release. Patients who are willing to undergo surgery are put on the waiting list, which means a waiting time of approximately 3 months. The trial investigator explains the aims, advantages and disadvantages of the trial to eligible patients at the orthopedic department's outpatient clinic. Patients who give informed consent will be allocated to one of the three trial groups. Recruited patients are assigned to a treatment group at the outpatient clinic according to a computer-generated randomization list. Immediately following the allocation the patients will receive the assigned treatment. In patients with bilateral symptoms the most symptomatic hand (as reported by the patient) will be included and in case both hands are equally symptomatic the dominant hand will be included. Patients will not be allowed to enter the trial more than once.

Recruitment to the trial according to the plan described above is believed to ensure the inclusion of a representative sample from the patient population residing in the catchment area. All patients are asked for informed consent before any study procedure is performed. The patients will be recorded in a screening/inclusion/randomization list.

### Ethics

This trial has been approved by the Ethics Committee at the Faculty of Medicine, Lund University (Nr 119-2008) and the Swedish Medical Products Agency (EU 2008-001871-31). The trial will be conducted in full compliance with the Helsinki Declaration.

### Randomization

A computer-generated randomization list of 120 items in blocks of variable sizes (unknown to the investigators involved in recruiting patients) is prepared by the statistician. Based on the list sequentially numbered sealed opaque envelopes containing cards with group assignments are prepared. These sealed envelopes marked with the patients' sequential numbers are kept at the orthopedic department's outpatient clinic. When a patient is enrolled and written informed consent obtained, the nurse opens the envelope with the lowest number and prepares the injection according to the card and then sign date, name and sequential number on the medication list. The nurse preparing the drug is responsible for putting the card in a new envelope marked with the sequential number. This card will be kept in a box with the study medication. As backup, a sealed envelope with the randomization database is kept, together with the study drugs, in the locked area reserved for drugs at the outpatient department. In case the blinding needs to be broken for a patient, the nurse will open the envelope and extract the information for that patient. The envelope will be signed with name and date and given to a monitor.

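### As most naturally read, the code-break rule has a clinic nurse open the full randomization list for one patient, which during recruitment would reveal every allocation still to come

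*Protocol article*

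**What the plan says.** The Randomization section of the protocol article describes three sets of envelopes.

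- **Allocation envelopes, one per patient.** They come from the statistician's list: "A computer-generated randomization list of 120 items in blocks of variable sizes (unknown to the investigators involved in recruiting patients) is prepared by the statistician". They are held on site: "These sealed envelopes marked with the patients' sequential numbers are kept at the orthopedic department's outpatient clinic". After written consent, "the nurse opens the envelope with the lowest number and prepares the injection according to the card".
- **Resealed card, one per treated patient.** "The nurse preparing the drug is responsible for putting the card in a new envelope marked with the sequential number". Its location is also given: "This card will be kept in a box with the study medication".
- **One envelope for the whole trial.** "As backup, a sealed envelope with the randomization database is kept, together with the study drugs, in the locked area reserved for drugs". The sentence goes on to place that area in the outpatient department.

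The code-break rule comes directly after the third item: "In case the blinding needs to be broken for a patient, the nurse will open the envelope and extract the information for that patient". The section then closes with "The envelope will be signed with name and date and given to a monitor".

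**The concern.** A code-break should disclose one patient's treatment and nothing else. Here the rule appears to send the nurse to a record of every patient's treatment, including patients not yet enrolled.

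The allocations still to come are what the rest of the section protects. Only the next numbered envelope is opened, only after consent, and the block sizes are withheld from recruiters. Once the full list has been opened in the same department, these safeguards no longer keep the remaining sequence hidden from everyone on site.

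The setting makes a leak costly. According to the Recruitment section, investigators at this clinic judge eligibility and whether severity warrants surgery, and they invite patients into the trial. According to the Follow-up section, the investigator also conducts the 5-week telephone interview and asks at 10 weeks whether the patient wants to go ahead with surgery. The two primary endpoints are the 10-week symptom score and the rate of surgery.

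**Working it through.** The plan states no figure on this point, so there is nothing to reproduce. The check is a reading of the text followed by a simple count.

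**Step 1: which envelope is meant?**

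| Feature of the text | Points to |
|---|---|
| The code-break sentence follows the database envelope directly and says *the* envelope | Database envelope |
| The nurse is to extract one patient's information, which suits a record of many patients; a single card needs no extraction | Database envelope |
| The database envelope is introduced as a backup, which implies that the patient cards are the primary record | Patient's own envelope |
| Each card is resealed under the patient's number, with no other stated use | Patient's own envelope |
| The opened envelope is signed, dated and given to a monitor | Either |

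The wording of the rule itself favours the database envelope. The surrounding arrangement leaves the other reading possible. Nowhere does the section assign code-breaks to the patient's own envelope.

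**Step 2: future allocations that become readable.**

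Input: list size 120 (Randomization). Let k be the number of patients randomized when the list is opened, whichever patient's code is being broken.

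Future allocations readable = 120 - k

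| k | Database envelope opened | Patient's own envelope opened |
|---|---|---|
| 1 | 119 | 0 |
| 30 | 90 | 0 |
| 40 | 80 | 0 |
| 60 | 60 | 0 |
| 90 | 30 | 0 |
| 120 | 0 | 0 |

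**Step 3: past allocations newly disclosed.**

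The list also shows k - 1 other treated patients. A nurse who prepared all those injections learns nothing new (0). A nurse who prepared none of them could learn up to k - 1, for example 39 at k = 40. The article does not say how preparation is shared among nurses, so the range is 0 to k - 1. In either case the information reaches a staff group that already handles allocations.

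**Step 4: sources left after one code-break.**

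The database envelope goes to the monitor. The resealed cards of all treated patients stay in the box with the study medication, so a later code-break for a treated patient still has a source on site.

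**The case against.** The strongest defence is that the sentence is only loosely worded. Resealing each card under the patient's number makes most sense as a code-break record, and the database is called a backup. On that view the plan already does the right thing, and the point is one of clarification. This stands in part: the database reading is an inference, though the better supported one. It does not remove the point, because an emergency instruction that is most easily read as an order to open the full list may be followed that way.

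Three stronger conclusions might be inferred, and the document does not support them.

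- **That one code-break newly exposes 119 of 120 allocations.** This counts past patients whose treatment the preparing nurses already know. Only the 120 - k future allocations are new to all of them.
- **That the only backup is used up, or that the rule works once.** The patient-level cards remain. The database envelope is the only whole-list record described at the clinic, but treated patients do not depend on it.
- **That selection or the primary endpoints would be biased.** The nurse opens the envelope and it then goes to a monitor. Nothing gives the list to the recruiting investigator, the blinded physical therapist or the patients. Bias would need a nurse to pass information on, and for past patients that possibility already exists under routine preparation.

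It is also fair to say that a condensed article need not explain resealing, replacement or who else holds the list. Those silences are not part of this point, which concerns only the rule that is stated.

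**Conclusion.** The point holds in limited form. As most naturally read, the stated code-break rule opens the complete randomization list at the recruiting clinic. If that happens during recruitment, 120 - k future allocations become readable to nursing staff, against none if the patient's own envelope is used.

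This rests on two assumptions: that the envelope in the rule is the database envelope, and that a code-break occurs before the 120th patient is randomized. The document gives no probability for a code-break, so the figures describe exposure if one occurs, not an expected loss. The harm is a weakening of allocation concealment. It is not a demonstrated bias in either primary endpoint. The change is worth making because the rule as stated undercuts the section's own safeguards and the means to avoid this are already in place.

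**What to change.** In the Randomization section, replace the code-break sentence with wording to this effect: to break the blind for a patient, the nurse opens only that patient's own resealed envelope bearing the sequential number; it is signed and dated on opening and passed to the monitor.

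For the full list, take one of two routes. Either hold it away from the recruiting clinic, for example with the statistician who prepared it, or keep it on site and state that it may be opened only if the patient's own envelope is missing. The first protects future allocations better. The second leaves some exposure in that rare case.

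The cost is one or two sentences and, on the first route, moving one envelope. The patient-level envelopes already exist and are kept with the study medication, so routine code-breaks should be no slower. The one downside is slightly slower access to the backup list if a patient's envelope is lost.

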### Interventions

Group A: 1 ml 40 mg Methylprednisolone (Depomedrol 40 mg/ml) + 1 ml 10 mg Lidocaine (Xylocain 10 mg/ml) + 1 ml saline (NaCl Bayer)

Group B: 2 ml 80 mg Methylprednisolone (Depomedrol 40 mg/ml) + 1 ml 10 mg Lidocaine (Xylocain 10 mg/ml)

Group C: 1 ml 10 mg Lidocaine (Xylocain 10 mg/ml) + 2 ml saline (NaCl Bayer)

The mixture of drugs is prepared by the nurse in the outpatient orthopedic department. This mixture of drugs is standard procedure for Methylprednisolone injection and all nurses have experience in performing this task. The drugs will be injected subfascially in the soft tissue of the carpal canal once by the investigator at baseline according to a previously described injection technique [17]. After injection, patients are instructed to use their hands normally as tolerated; no instructions are given regarding specific activity modifications or splint use.

### Evaluations

At baseline and the last follow-up (Table 2) median nerve conduction testing of both hands is performed. The measurements include median nerve motor distal latency and sensory conduction velocity across the carpal tunnel, median nerve index finger-wrist sensory latency, or ring finger-wrist median-ulnar sensory latency difference.

**Table 2 T2:** Patient visits in the trial, data collection and outcome measures

	Pre-screen	Baseline	5 wk +5 d	10 wk ± 7 d	12 wk^† ^± 7 d	24 wk ± 7 d	52 wk ± 7 d
Diagnosis, inclusion & exclusion criteria	X						
Demographics		X					
Randomization		X					
Physical examination*		X		X		X	X
Nerve conduction testing		X					X
Outcome questionnaires		X	X	X		X	X
Rate of surgery					X	X	X
Sick-leave report		X	X	X		X	X
Adverse events		X	X	X		X	
Study medication		X					
Concomitant medication		X	X	X		X	

*Two-point discrimination, monofilament test, grip and pinch strength

^†^Surgery in participants choosing to have surgery

At baseline and at three follow-up occasions a physical examination is performed by the same physical therapist with extensive experience in hand therapy. Semmes-Weinstein monofilament and two-point discrimination tests of sensation are performed on the radial and ulnar aspects of each finger; two-point discrimination testing starts with a distance of 4 mm that is successively increased by 2 mm until the correct tactile discrimination is recorded. Grip strength and 3-point pinch strength are measured with the Baseline dynamometer and pinch gauge (Chattanooga Group, Hixson, Tennessee, USA), respectively (three trials for each hand). Before examination, the patients are instructed not to discuss their treatment with the assessor and will have their palms covered with a dressing to conceal possible scar after carpal tunnel release. The assessor is thus blinded to whether the patient had or had not undergone surgery after the injection. At the 10-week examination the success of blinding is evaluated by asking the examiner and patient to record whether they think the patient had received active treatment. After the 52-week physical examination the patient will proceed to nerve conduction testing keeping the same palm dressing so that the examiner also will be blinded.

### Follow-up

At the *Baseline *visit, demographics, earlier and ongoing disease, and concomitant medication are recorded. The baseline data include weight, height, and smoking and employment status. The patient completes a questionnaire that includes demographic data, the CTS symptoms severity scale, the 11-item disabilities of the arm, shoulder and hand (*Quick*DASH) questionnaire, and the SF-6D. A physical examination is performed.

At *5 weeks *after injection a telephone interview is conducted by the investigator and the patient is asked to complete the CTS symptoms severity scale and concomitant medication and adverse events (AEs) will be recorded.

At *10 weeks *after injection the patient is examined by the physical therapist. The investigator asks the patient whether she/he wants to proceed with surgery as planned at 12 weeks after injection or whether the patient has experienced adequate symptom relief that she/he wants to continue follow-up and not have the planned surgery at this stage. An evaluation similar to the baseline evaluation is performed and the indication for surgery is recorded. The patient completes the CTS symptoms severity scale. Concomitant medication and AEs are recorded. Possible use of a wrist splint since the injection and its frequency is recorded.

At 12 weeks the patient who had chosen to have surgery is operated on as scheduled.

At *24 weeks *after injection the patient is examined and asked to complete a questionnaire including the CTS symptoms severity scale, *Quick*DASH, and the SF-6D as well as to rate satisfaction with the treatment on a visual analog scale from 0 (very dissatisfied) to 100 (completely satisfied). Concomitant medication and AEs are recorded.

At *52 weeks *after injection the patient is asked to attend a physical examination and nerve conduction tests and complete the questionnaires.

